### Reliability and validity

Providing a study identifier on each information leaflet means that only one participant can use it to register onto the study and will ensure that participants are coming from one of the participating services. No recruitment will be done via other methods.

Using a minimisation method for randomisation will reduce the risk of selection and allocation bias. It will also ensure that we balance demographic factors across the two groups. It is not possible to blind participants to which group they have been assigned. However, clinicians will not be informed about whether participants have consented to participate, or which group they were allocated to. This is done to maintain the treatment as usual care of all participants. The feasibility of clinician blinding will be assessed as part of the study evaluation.

More than one researcher will code qualitative interview and focus group data, and inter-rater reliability will be measured. Coding frames will be discussed and agreed by wider members of the research team following guidance from qualitative data analysis methodology.^47^

### Ethics and dissemination

Participants will receive information about the study via an information leaflet which includes links to further information about the study and the contact details of the research team. Participants will give informed consent before participating in the study. The study team will signpost to appropriate resources and support during the study and will monitor and flag adverse events (eg, severe mental health difficulties) resulting from study participation. Participants are able to withdraw from the study by informing the research team at the University of Sheffield. This will not impact the care they receive from their diagnostic setting.

The study protocol was reviewed by East Midlands—Nottingham 2 Research Ethics Committee and given ethical approval on 18 March 2025. The study has been registered on ISRCTN (ISRCTN10283350) and has been adopted onto the NIHR study portfolio (CPMS: 66984). Any protocol modifications will be submitted by amendment via the NIHR’s IRAS procedure.

The results of the study will be disseminated via reports to the funder (NIHR), a peer-reviewed journal paper and academic conferences. We will email a summary report of findings to study participants and will invite study participants to an information dissemination event at the end of the study. Links to reports and a lay summary will be provided on the research group’s website: https://sharl.sites.sheffield.ac.uk/home Anonymised study data will be deposited in the University of Sheffield’s data repository at the end of the study (eg, outcome scores on mental health measures, coding frames for qualitative data). This will not include responses to the strengths and needs assessment, demographic data or interview transcripts.

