The study will also evaluate the acceptability and feasibility of the trial design in preparation for a future definitive randomised control trial (RCT). The UK’s Medical Research Council’s framework for evaluating complex interventions^34^ highlights the importance of piloting prior to larger efficacy trials being carried out. This identifies potential problems which could lead to underpowering in larger trials and provides estimates for trial sample sizes. Acceptability will be evaluated in interviews with participants and focus groups with clinicians. The feasibility of the proposed recruitment, randomisation and data collection methods will be evaluated against a list of progression criteria before planning for a future trial.

Specifically, the research questions are

RQ1a: Are the proposed recruitment, randomisation and data collection methods acceptable and feasible for use within NHS adult autism diagnostic services?

RQ1b: Is the ICF CoreSets for Autism Strengths and Needs Assessment acceptable for use by autistic adults on receipt of an autism diagnosis?

RQ1c: What are the potential benefits or harms of completion of the ICF CoreSets for Autism Strengths and Needs Assessment?

The secondary aim is to gain a thorough understanding of the characteristics and mental health status of the populations receiving autism diagnoses in these clinical settings. We will use mental health and quality of life (QoL) outcome measures to answer the secondary research question:

RQ2: What are the demographics and current mental health status of adults being diagnosed in NHS services?

Mental health measures will also be used to monitor for adverse events arising from study participation. They will also provide preliminary data on whether the strengths and needs assessment improves well-being outcomes and how feasible it is to use these measures to measure efficacy in a larger trial.

The study will be reported according to Consolidated Standards of Reporting Trials guidelines for reporting randomised pilot and feasibility trials.^35^ If effective, the ICF CoreSets for Autism Strengths and Needs Assessment have the potential to be implemented in NHS diagnostic services as a standardised approach to providing post-diagnostic support for autistic adults.

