### Study procedures

Service users who receive a diagnosis of autism and meet the other eligibility criteria (18+ years old, no diagnosis of intellectual disability) will be given information about the study (written information leaflet, verbal information) by their diagnosing clinician which includes links to access further information about the study and contact details for the research team at the University of Sheffield. This will be given alongside other standard care information (eg, signposting to resources, information about their service’s post-diagnostic provision) at the appointment where they receive their diagnosis. The full information sheets for the study have been provided in standard and Easy Read/Plain English versions. Participants will have 4 weeks from the date of their diagnosis to decide whether they would like to participate in the study. They will be able to access a form to consent to participate and to provide their contact details via the links provided in the information leaflet.

Participants will be emailed a link to complete a short demographic questionnaire (age, gender, ethnicity, diagnosing service, date of diagnosis). Following this, they will be randomised into either the assessment group (n*=*36) or the treatment as usual group (n*=*36) by the research team at the University of Sheffield. This will be done using a minimisation approach which allows demographic factors to be balanced across groups in ongoing recruitment. This will be done using software developed by researchers at the University of York^36^ and will balance three factors (gender, age, ethnicity) with two levels for each factor (male/female, under/over 40, white/non-white) in each study arm. All participants will continue with the standard care offered by their clinical site during the study. This may include signposting to resources, follow-on appointments and psychoeducational input. It is not possible to blind participants to group allocation. However, clinicians will not be informed about individual participation or group allocation.

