Both groups will complete online QoL and mental health questionnaires at baseline (T1) and at 3 months follow-up (T2). Only the assessment group will be asked to complete the strengths and needs assessment. A link to complete the strengths and needs assessment will be emailed immediately after baseline measures are completed. Participants will be told that they can email the researcher with any questions about the assessment or to provide support during the completion process. They will also be told that they can do the assessment in as many sittings as they choose to (responses are saved on the platform continually) and that they can complete the assessment over a 2-week period.

Participants will receive voucher payments of £20 for completing their T1 measures and £10 for completing T2 measures. Participants who do not complete measures will receive a reminder email with contacts for the research team at the University of Sheffield and links to support services.

A subsample of 12 participants (four from each service: two from the Assessment group and two from the treatment as usual group) will also be invited to take part in an interview after T2. They will be provided with additional information for these interviews and will be asked to consent to take part. The interviews will be held mainly online, although some will be hosted in the diagnostic services, if participants prefer, and services have capacity to offer this. The interviews will follow a semi-structured schedule which will cover the acceptability and feasibility of the study procedures and the strengths and needs assessment, any barriers or facilitators to trial participation, any adverse effects of participation and their personal experiences of post-diagnostic support. Interviews will last for around 30 min and will be recorded and transcribed verbatim. Participants will receive voucher payments of £20 for taking part in an interview. Participating clinicians and administrators (involved with the set up or running of the study at each site) will be invited to take part in a focus group at each diagnostic service following the 6-month data collection period. Figure 1 shows the movement of participants through the study.

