### Primary outcome measures

The primary study outcomes are the acceptability and usability of the strengths and needs assessment, and the acceptability and feasibility of the trial procedures. Acceptability of the strengths and needs assessment will be measured using a single item from the TFA^30^: ‘How acceptable was the assessment to you?’. This is answered on a 5-point Likert scale from completely unacceptable to completely acceptable. The SUS^29^ will assess the usability of the assessment. This is a 10-item questionnaire answered on a 5-point Likert scale. Responses are summed and scaled to give an overall usability score which can be used to categorise interventions (eg, poor, ok, good, excellent). The SUS has demonstrated reliability and concurrent validity with measures of perceived and objective usability.^37^

Completion times for the strengths and needs assessment and outcome measures will be recorded and reported using sample medians. For those who drop out, time on task until drop-out will be recorded and reported.

The acceptability and feasibility of the trial procedures will be measured by collecting procedural data from the participating sites (eg, the number of participating clinicians, clinician time required to distribute participant invitations, service user eligibility rates). The study team at the University of Sheffield will collect data on recruitment rates and representativeness, adherence rates for the outcome measures and the attrition rate in each arm of the study. Participant interviews and clinician focus groups will also be used to evaluate the acceptability and feasibility of study procedures, barriers and facilitators to study participation, perceived value in the strengths and needs assessment, and any adverse events associated with the study.

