### Secondary outcome measures

The secondary outcomes are the demographics (age, gender, ethnicity) and current mental health status of the autistic adults recruited into the sample. This will be used to show the representativeness of the sample and levels of well-being in the sample. It will also give some preliminary data around whether the strengths and needs assessment has an impact on well-being levels and whether it would be feasible to measure mental health outcomes in this way in a larger trial.

Mental health/QoL outcomes will be measured using the following:

The 5-level EQ-5D^38^ is National Institute for Health and Care Excellence’s preferred measure of health-related QoL in adults^39^ and is necessary for health economic evaluation to assess quality-adjusted life-years.The Patient Health Questionnaire-9^40^ (PHQ-9) measures levels of depression, self-harm and suicide risk. The PHQ-9 has good sensitivity and specificity for detecting depressive disorders.^41^ This outcome measure will be used to monitor for adverse events during the study. If participants score in the severe range (20–25) on the PHQ-9, this will trigger a letter to be sent to their GP.The Generalised Anxiety Disorder-7 (GAD-7)^42^ measures levels of anxiety. The GAD-7 has good sensitivity and specificity for detecting generalised anxiety, panic, social anxiety and post-traumatic stress disorders.ReQoL-10^43^ is an important measure to support future health economic evaluation. This estimates utilities and hence QALYs and is now part of the core value set for mental health conditions.

These mental health and QoL measures will be collected at T1 and T2 (3-month follow-up). The questionnaires will be hosted online using Qualtrics^44^ and participants will be emailed links to access them. A previous trial^31^ suggests that these questionnaires will take between 10 and 20 min to complete at each timepoint.

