### Data analysis

Descriptive data for all demographic variables will be presented by trial arm to provide an overview of the cohort of participants recruited to the study, to evaluate the group allocation methods and to demonstrate the representativeness of the sample. Means and SD will be reported for the QoL and mental health measures. These will be compared with clinical cut-offs to indicate levels of well-being in the sample.

Eligibility rate, recruitment rate, completion rates and times for the strengths and needs assessment and the outcome measures will be reported descriptively. Sample medians will be used as an estimate of average completion times. CIs will indicate completion time variance.

Participants will be given 2 weeks to complete the strengths and needs assessment and the QoL/mental health measure questionnaire. After 1 week, they will be sent a reminder and offered support if they need it. After 2 weeks, they will be considered ‘lost to contact’ and will be sent a debrief form with links to support organisations. The number of participants ‘lost to contact’ or withdrawn will be recorded as part of the trial evaluation. If participants start but do not complete the strengths and needs assessment, we will record the time they spend on the assessment and the proportion completed. Any data previously given by participants who are ‘lost to contact’ or withdraw will still be analysed unless participants ask us to withdraw their data.

Preliminary effectiveness of the strengths and needs assessment will be assessed using mixed model analyses of covariance. These analyses will determine whether QoL (assessed using EQ-5D-5L and ReQoL-10) and mental health (assessed using PHQ-9 and GAD-7) changes between baseline and 3 months post-intervention are affected by allocation to the assessment/TAU group. The analyses will statistically control for demographic variables and clinical site. Effect size will be reported using partial eta-squared which will inform the sample size calculation for the definitive trial (RCT).

Qualitative data from the interviews and focus groups will be analysed using NVivo.^45^ Questions pertaining to acceptability and feasibility of the trial procedure will be analysed using thematic content analysis.^46^ Experience of post-diagnostic service provision more generally will be analysed using a reflexive thematic analysis approach.^47^

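### Adverse events are defined by presumed cause in some sections and by occurrence in another; the cause-based wording would not give a fair comparison of harms between arms

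*Protocol article*

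**What the plan says.** The protocol article describes adverse event monitoring in several places, in different terms.

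- Ethics and dissemination: the study team "will monitor and flag adverse events (eg, severe mental health difficulties) resulting from study participation".
- Introduction: "Mental health measures will also be used to monitor for adverse events arising from study participation".
- Study procedures: the interviews with 12 participants cover adverse effects of taking part.
- Primary outcome measures: the interviews and clinician focus groups are used to evaluate, among other things, "any adverse events associated with the study".
- Secondary outcome measures, on the PHQ-9: "This outcome measure will be used to monitor for adverse events during the study", followed by "If participants score in the severe range (20–25) on the PHQ-9, this will trigger a letter to be sent to their GP".

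On who knows what: the research team at the University of Sheffield carries out the allocation, and the link to the assessment is emailed to one arm only. For participants, "It is not possible to blind participants to group allocation". Clinicians are not told who takes part or in which arm. No blinding of the research team is described.

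On measurement: both arms complete the same mental health and quality of life questionnaires at T1 and at T2 (3 months). Data analysis tests whether change in these scores "are affected by allocation to the assessment/TAU group".

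**The concern.** RQ1c, placed under the primary aim, asks about potential benefits or harms of completing the assessment. Everyone enrolled has just received a diagnosis, at a time the Discussion itself describes as possibly overwhelming, so distress and crises unrelated to the assessment are plausible in both arms. The randomised control arm is there to show that background.

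It can do so only if events are recorded in the same way in both arms. If an event must be thought to result from participation before it is flagged, the count in each arm depends on attribution as well as occurrence. A crisis after the 265-item assessment can be put down to the assessment, or equally to the recent diagnosis and left out. The same crisis in a control participant has no assessment to be put down to. The distortion could exaggerate a harm or hide one.

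**Working it through.** No figure in the plan depends on this point, so the check is a comparison of the texts, with simple counts where they help.

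**1. Is there one definition?** No. The Introduction and Secondary outcome measures both speak of adverse event monitoring through the mental health measures. The Introduction limits it to events arising from participation. Secondary outcome measures applies it to events during the study. A severe PHQ-9 score in someone whose distress clearly has another cause counts under the second wording and not under the first. Ethics and dissemination follows the first, and gives severe mental health difficulties as its example. The interview and focus group wording is also attributional, but there participants and clinicians give their own views, so it is not a filter applied by the team.

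**2. Would the cause-based wording treat the arms alike?** No. Monitoring is assigned to the study team. The research team allocates and only one arm is sent the assessment link, so on the text as it stands the team can know the arm. Control participants complete the questionnaires but not the assessment. The set of things an event could be attributed to therefore differs by arm, by design.

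**3. What stays comparable?** PHQ-9 and GAD-7 are self-completed in both arms at the same two timepoints, and change is analysed by allocation. The PHQ-9 severe-range trigger is a score threshold that names no arm and needs no causal judgement. Severe-range counts by arm at T2 can be produced from data already planned.

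**4. What do those scores not cover?**

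- Timing. The assessment link is sent after the T1 measures are completed, so T1 cannot show harm from the assessment. T2 is the only scheduled score after it. Taking 3 months as about 13 weeks from T1 and the 2-week completion window, someone who finishes at the end of the window has 13 − 2 = 11 weeks before T2, and someone who finishes at once has about 13. An episode that resolves in that interval may leave no trace in the T2 score.
- Missing T2. Participants who do not respond are classed as lost to contact and have no T2 score. The Discussion anticipates that attrition may be higher in the control arm.
- Form of analysis. Data analysis reports means and SDs and models change. A few individual crises can disappear in a mean.
- Unequal contact. Assessment-arm participants are told they can email the researcher with questions about the assessment or for support in completing it, which gives that arm an extra route by which an event may come to light. Clinicians, not told who is taking part, cannot readily report events to the trial.
- Interviews. 3 sites × 2 = 6 people per arm, out of 36, so 6/36 or one in six.

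Events in these gaps depend on the flagging rule, which is where the cause-based wording applies.

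**The case against.** The strongest reply is that the most operational adverse event text is the PHQ-9 paragraph in Secondary outcome measures, which has no causal condition, and that the phrase in Ethics and dissemination is one summarising clause. On that view the trial already records severe mental health difficulties identically in both arms, and detailed recording and relatedness procedures belong in the full protocol, which is not shown. Controls also have some exposure: they complete four instruments twice, including one covering self-harm and suicide risk, so harm attributable to participation is possible in that arm too.

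Much of this stands. The absence of detailed procedures from the article is not a finding. A reader might infer that control-arm events cannot be compared with the assessment arm's at all. The documents do not support that, because T2 scores and severe-range PHQ-9 results are available by arm whatever the cause. A reader might also infer that the plan gives an unblinded team the deciding judgement on causality. It does not say so: who judges relatedness is not stated, and the lack of team blinding is an inference from who allocates and who is sent the link. Nor does the text say that reported counts will exclude unrelated events.

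What the reply does not remove is that two sections state a cause-based limit and a third states the opposite. That is a conflict in what is written, and the PHQ-9 does not reach the gaps listed above.

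**Conclusion.** The concern holds in limited form. The adverse event wording is inconsistent, and the version in the Introduction and in Ethics and dissemination, if applied as written, would filter flagged events by presumed cause and so give no fair comparison between arms for RQ1c. The comparison of T2 questionnaire scores by arm is unaffected by that filter. The loss is confined to events those questionnaires miss, events that resolve before T2, and people without a T2 score.

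The size cannot be given, because the documents contain no event or attribution rates; the direction could go either way. The conclusion assumes that whoever flags events knows the allocation, which the text implies but does not state, and that the full protocol does not already settle the definition. With 36 per arm, one event is 1/36, or about 2.8 percentage points, so even well-recorded counts are descriptive and could not establish or exclude harm. The wording should be corrected because a harms question sits under the primary aim and the correction is cheap.

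**What to change.** Reconcile the Introduction, Primary outcome measures, Secondary outcome measures and Ethics and dissemination to one definition: untoward events during the study, from allocation to T2, are recorded in both arms whatever their presumed cause. Ask about them in the same way in both arms, for example with one identical item in the T2 questionnaire. Record relatedness afterwards as a separate field, not as a condition for recording. The interviews can still ask what participants think caused an event.

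Report all-cause counts by arm first, including the number with a severe-range PHQ-9 score at T2, with the number who returned T2 as the denominator. Report related events second. Keep both descriptive.

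The cost is an amendment to the wording, one extra question, and a longer list of events, most of them probably unrelated. If the T2 item can no longer be added, the severe-range counts by arm still need no new data.
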